### Aims of the study

Primary aim of this study:

1. To evaluate the changes in the intestinal perfusion and oximetry determined by feeding in VLBW infants fed by 3 hours nasogastric nutrition (CN) *versus* infants fed by bolus nutrition (BN).

Secondary aims of the study:

2. To compare if changes in the intestinal perfusion and oximetry induced by feeding are different between IUGR and NON-IUGR infants.

3. To compare growth and nutritional status of the 2 groups by randomized arm.

4. To test if changes in intestinal oximetry and perfusion can be reliable predictors of feeding intolerance (days necessary to achieve full enteral feeding)*.*

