### Endpoints

The endpoint for the primary aim will be the cross-over difference of CSOR values, measured with NIRS before and at the end of the randomized feeds.

Aims 1 to 4 will be pursued analysing the following endpoints:

· The cross-over difference of CSOR values and of rSO2s values (i.e. the splanchnic saturation slope) in IUGR and non-IUGR infants.

· Growth and nutritional status will be measured by weight, length and head circumference. Main comparison will be between measures at randomization and at achievement of full enteral feeding. The growth at 28 days of life and at 36 weeks of gestational age will also be compared with the appropriate standard growth curves.

· The difference in the CSOR values pre- and post- feeding will be compared with the baseline CSOR value and the baseline Doppler flow velocimetry (both measured within the first 72 hours of life)*.*

· Comparison of the time needed to reach full enteral feeding (i.e. days from randomization till enteral intake of 160 ml/kg/day of formula or fortified human milk) by randomized arm;

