Measurements of body weight, length and head circumference will be performed at predefined times: at birth, at the beginning of MEF, on the randomization day, at the achievement of full enteral feeding, at 28 days of life and at 36 weeks of gestational age.

Parameters of feeding tolerance are those routinary used in the NICU (maximum gastric residual and residual appearance). The enteral nutrition will be discontinued or carried on according to our feeding protocol.

The follow-up will end at the achievement of a full enteral feeding, enteral intake of 160 mL/Kg/die or at 28 days of life, whichever occurs later. Patients may drop-out before this intended end because of the following withdrawal causes:

Withdrawal of the consent by the relatives

Severe skin reaction due to the skin probe

Transferral to another hospital

Death

After study end, patients will be fed according to the standard protocol of our Unit.

During the study, recommended diagnostic and therapeutic procedures are those usually performed as standard care in our Unit.

No new special measure for safety is planned since all the diagnostic and therapeutic procedures are part of the standard approach to the VLBW infant in our Unit.

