#### Statistical analysis

The primary aim of the study is to compare the impact on intestinal perfusion of 2 different nutrition modalities, bolus (BN, Group A) versus a 3-hour nasogastric nutrition (CN, Group B). The impact on intestinal perfusion is defined as the difference between pre- and post-prandial CSOR values measured with NIRS 30 minutes before feeding and at the expected peak after feeding (3 hours in CN and 30 minutes in BN). Pre- and post-prandial CSOR values will be calculated as the mean of 5-minute NIRS evaluations about the intended time-point (e.g. for baseline CSOR measurement, 2.5 minutes before and 2.5 minutes after the 30th minute before start of the randomized feed). Given that the study is a cross-over study, each infant will be evaluated both for CN and BN and the cross-over CSOR difference will be the primary endpoint.

As a secondary analysis, the cross-over difference of CSOR values as well as that of SO2s values (i.e. the splanchnic saturation slope) will be analysed comparing intra-uterine growth (IUGR vs. non-IUGR).

The impact of the 2 nutrition modalities on CSOR will also be studied in a multivariable context, adjusting for factors including the baseline CSOR value, the baseline Doppler flow velocimetry (both measured within the first 72 hours of life) and the intra-uterine growth (IUGR vs. non-IUGR).

Other secondary analyses include:

· Comparison of the time needed to reach full enteral feeding (i.e. days from randomization till enteral intake of 160 mL/Kg/day of formula or human milk) by randomized arm;

· Comparison of growth as measured by weight, length and head circumference by randomized arm. Main comparison will be between measures at randomization and at achievement of full enteral feeding. The growth at 28 days of life will also be compared with the appropriate standard growth curves.

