The primary end-point analysis as well as all secondary analyses regarding randomized patients will be based on the ITT (intention-to-treat) principle. Comparisons of the two arms accounting for deviations from the assigned arm (analyses by “performed treatment”) will also be added to this main analysis. The primary endpoint will be analyzed with a two-tailed matched pairs t-test, after checking of appropriateness of assumptions. In particular, checking will concern the normality assumption, since period effect and cross-over effect appear both very unlikely in this study. Should normality be not adequate, non-parametric test such as the Wilcoxon signed ranks test will be applied [20]. An appropriate generalized linear model will be used to investigate the relationship between the CSOR cross-over difference and the candidate covariates. Should any raw CSOR observations be missing (e.g. NIRS instrument failed to measure or to save measurements), their estimation via imputation or other appropriate methods will be taken into account. The comparison of growth variables by randomized arm will be performed with either the two-tailed t-test or a non-parametric alternative (e.g. Mann–Whitney test), should the normality assumption be not reasonable. The time from randomization till achievement of the full enteral feeding will be analysed with the Kaplan-Meier estimator, in which full enteral feeding as defined in the protocol will be considered as the sole ‘event’, while censoring will occur for withdrawal for any cause. Standard errors will be computed according to Greenwood formula and the log-rank test will be used for univariate comparisons.

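### The main growth comparison by arm is made over the time to full enteral feeding, itself a by-arm outcome, with no allowance for its length; separately, the 36-week growth measure conflicts with the end of follow-up.

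*Protocol article*

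**What the plan says.** Secondary aim 3 in Aims of the study is "To compare growth and nutritional status of the 2 groups by randomized arm". Endpoints and Statistical analysis both define the main growth contrast in the same words: "Main comparison will be between measures at randomization and at achievement of full enteral feeding". On the test, Statistical analysis says: "The comparison of growth variables by randomized arm will be performed with either the two-tailed t-test or a non-parametric alternative". It mentions neither a rate per day nor the number of days elapsed.

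The same interval is a separate by-arm outcome, defined as "days from randomization till enteral intake of 160 mL/Kg/day of formula or human milk" and analysed by Kaplan–Meier and log-rank. Aim 4 treats days to full feeding as the measure of intolerance: "feeding intolerance (days necessary to achieve full enteral feeding".

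At fixed ages, Endpoints says: "The growth at 28 days of life and at 36 weeks of gestational age will also be compared with the appropriate standard growth curves". Statistical analysis repeats this for day 28 only. The measurement schedule, in the Methods text under Stratification, includes 36 weeks of gestational age. The same text says that follow-up "will end at the achievement of a full enteral feeding, enteral intake of 160 mL/Kg/die or at 28 days of life, whichever occurs later".

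**The concern.** The end of each infant's growth window is an event after randomisation, and the allocated feeding method may move it. A total gain over that window mixes how fast the infant grew with how long it took to reach 160 mL/kg/day. Infants in an arm that advances more slowly are observed for longer. At the same growth velocity they gain more weight, length and head circumference, and poorer tolerance could then be read as better growth. The trial sets out to test whether time to full feeding differs by arm, so a difference cannot be assumed away.

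A fixed-time measurement would not have this problem. Day 28 is already measured within follow-up, but the comparison described for it is with standard growth curves, and no fixed-time contrast between arms is spelled out.

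The second issue is one of timing. A growth endpoint at 36 weeks is listed and scheduled, yet the follow-up rule would normally have ended before then, and the analysis section leaves it out. Different readers could collect and report different things.

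**Working it through.** **The plan's own figures.** The article gives no effect size, power or expected growth rate for growth. Its only power figures (Table 1) concern CSOR. A two-sided paired t-test with n = 20, df = 19 and noncentrality (difference/σ) × √20 gives 84.4%, 80.7% and 78.7%, against the stated 84%, 80% and 78%. Table 1 reproduces and has no bearing on this point.

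**Length of the window.** Randomisation is at 100 mL/kg/day, full feeding is 160 mL/kg/day, and the increase is 20 mL/kg/day if tolerated (Methods and design). The minimum is (160 − 100)/20 = 3 days. Any setback lengthens it.

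**Extra gain per extra day at equal velocity.** Assumed, because the documents give no values: weight 1.1 kg, velocity 10–20 g/kg/day.
- Per extra day: 1.1 × 10 = 11 g to 1.1 × 20 = 22 g.
- For 3 extra days: 33 g to 66 g.

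**False-positive rate of the named t-test on total gain.** Assumed: 10 infants per arm; days to full feeding = 3 + a gamma variable; velocity 15 g/kg/day with CV 25% in both arms; weight 1.1 kg, SD 0.2. The gamma shape sets the spread and was varied over 1, 2, 4 and 8.

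| Mean days, arm v arm | Mean gap in gain | Rejection at two-sided 5% |
|---|---|---|
| 5 v 5 | 0 g | about 5% |
| 5 v 5.5 | about 8 g | 6–9% |
| 5 v 6 | about 16 g | 8–19% |
| 5 v 8 | about 50 g | 27–74% (27, about 45, 62, 74 for shapes 1, 2, 4, 8) |

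For 5 v 8 days and shapes 1 to 4, Mann–Whitney gave 26–57%, so the non-parametric alternative does not remove the problem. A simulation with other assumptions (1,200 g, SD 200; 15 g/kg/day, SD 4; SD of days 2) gave 32% for 4 v 6 days and 57% for 5 v 8. Testing velocity kept rejection at about 5% throughout. That follows from the model, in which velocity is independent of duration.

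**Timing of 36 weeks.** Inputs: gestational age at most 25 weeks 6 days (Inclusion criteria) and the follow-up rule.
- 36 × 7 − (25 × 7 + 6) = 252 − 181 = day 71, which is 71 − 28 = 43 days after day 28.
- For birth at 25 weeks 0 days: 252 − 175 = day 77, which is 49 days after day 28.
- Assuming 20 mL/kg on day 4 and a rise every day, full feeding is reached on day 4 + (160 − 20)/20 = day 11. Follow-up would then end at day 28.

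The 36-week measurement therefore falls inside follow-up only for an infant not yet at full feeding by about day 71.

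**The case against.** **The text does not say absolute gain.** It names measures at two times and a test, and a rate or z-score change is not excluded. That is fair, and the bias applies only to a total. But the article fixes the window and names the test with no allowance for duration, so a total is the natural reading.

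**The window has a rationale.** Allocated feeding runs from randomisation to full feeding, so this is the exposure period, and time to full feeding is reported alongside. This justifies looking at the period, but a difference in duration shown in another table does not correct the growth test.

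**Day 28 may be meant by arm.** In Statistical analysis the day-28 sentence sits under the bullet on growth by randomised arm. That reading is possible, but the comparator named is the standard curves.

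Three stronger readings are tempting, and the documents do not support them:
- *That the growth result will point the wrong way, or is false-positive about half the time.* The article gives no expected time to full feeding. A 3-day gap equals the whole uncomplicated window, and the rate depends heavily on the assumed spread. Poorer tolerance could also slow growth and offset the artefact, which the simulations do not model.
- *That the 36-week endpoint cannot be collected.* The schedule lists it explicitly, and an infant reaching full feeding on day 71 or later would still be in follow-up. The fault is a contradiction.
- *That the growth tests wrongly ignore IUGR stratum and size at randomisation.* Adjustment is detail commonly left to an analysis plan, and comparing measures at two times already uses the starting size.

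**Conclusion.** The point holds in two parts.

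First, the main growth contrast is tied to an interval that is itself a by-arm outcome, and the named tests take no account of its length. A total gain then favours the slower arm whenever the arms differ in time to full feeding. The size rests on assumed growth rates, weights and spreads. It is negligible if the times are equal, modest for a 1-day gap, and potentially serious for a 3-day gap. The direction of the artefact is clear. How likely it is to reverse a conclusion is not known.

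Second, Endpoints, the measurement schedule, the follow-up rule and Statistical analysis disagree about 36 weeks. This rests on date arithmetic from the gestational-age limit as written. For infants born at 32 weeks or later the conflict would vanish (36 × 7 − 32 × 7 = 28 days), but the stated limit excludes them.

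Only secondary aim 3 is affected, in a study that describes itself as explorative. The primary CSOR endpoint and its power are untouched.

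**What to change.** 1. In Endpoints and Statistical analysis, make the main by-arm comparison growth velocity from randomisation to full feeding: g/kg/day for weight, cm/week for length and head circumference. State that this removes the direct effect of duration but that the window still depends on an outcome.
2. Add a by-arm comparison at a fixed time, adjusted for the measure at randomisation and IUGR stratum. Day 28 serves for infants randomised sufficiently before it. It does not serve for those randomised near or after it, since randomisation has no age limit. A fixed interval after randomisation, using routine chart weights, covers all infants.
3. Reconcile 36 weeks across Endpoints, the measurement schedule, the follow-up rule ("or at 28 days of life, whichever occurs later") and Statistical analysis. Either extend anthropometric follow-up to 36 weeks from routine chart data, or delete the 36-week endpoint.

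The cost is wording, plus retrieval of routine measurements from the chart for the fixed-interval comparison and for 36 weeks if it is kept. No feeding rule or other clinical procedure changes.

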### Statistical considerations

#### Randomization

Randomized interventions are described in Section ‘Methods and Design’. This section summarizes procedures and methodology, which will be adopted**.**

Patients eligible to randomization: all VLBW infants enrolled and eligible to the study, either IUGR or non-IUGR, who fulfil the following requirements:

1. achievement of 100 mL/kg/day of enteral nutrition;

2. adequate ventilation i.e. infants who are not intubated and not in-cPAP with a FiO2≥50% at the achievement of 100 mL/Kg/day of enteral nutrition;

3. no NEC;

4. Informed consent from parents or guardians.

When to randomize:

a. * After *achievement of 100 mL/kg/day of enteral nutrition in presence of adequate ventilation (see point 2 above)

Modalities of randomization:

b. Logistics: investigators will ask for randomization by access to a specific software which will provide the assigned arm, after check on the eligibility criteria.

c. Methodology: randomization will be stratified (IUGR vs non-IUGR) and by blocks: the random assignment will be produced by an automatic procedure Ranlist [19] and will be based on random permuted blocks of small size, given the limited number of infants expected in each stratum.

**Randomization refusals:** if parents or guardians do not agree with randomization, patients will be excluded from the study and should be fed according to nutrition procedure regarded as the most appropriate for the child based on the Unit standard policy.

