### Sample size

This single-center study will recruit patients for 2 years (24 months) since official opening. The expected accrual is about 20 VLBW infants, either IUGR or non-IUGR. The power calculations below are based on a two-tailed t-test with I-type error α=0.05 and show the power that the 20-patient study will achieve under various differences in CSOR from the ‘baseline’ impact observed under BN. On the basis of previous studies [21] this is expected to be 0.10 (mean of CSOR pre-post prandial difference), while various hypothesis are made about its standard deviation, σ_CSOR_

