### Sample size: 20 infants

The power calculations in different scenarios show that with 20 patients the study will achieve a good power in presence of a cross-over difference of at least 0.07 (Table 1).

**Table 1 T1:** Impact on CSOR under BN=0.10

**σ**_**CSOR**_	**CSOR cross-over difference**	**Power**
0.10	0.07	84%
0.15	0.10	80%
0.20	0.13	78%

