## Discussion

This is an explorative study. Evaluations of intestinal oximetry and superior mesenteric artery blood flow after the feed may help in differentiating how the feeding regimen alters the splanchnic blood flow and oxygenation and if the changes induced by feeding are different in IUGR versus NON IUGR infants.

We postulate that TOI will be altered in the vascular bed when blood flow is decreased; the resultant acidosis in poorly perfused tissues may also further increase the dissociation of oxygen from haemoglobin and increase the portion of reduced haemoglobin detected with NIRS. This condition may be present in IUGR infants and this condition may alter feeding tolerance thus requiring a longer time to achieve full enteral feeding and increasing the episodes of feeding intolerance.

Gut perfusion may depend on the way of administering feeding, bolus or continuous nutrition, so this study may suggest which is the best way to feed VLBW infants.

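### Feed order is randomised within IUGR strata, but the primary paired t-test has no stratum term, so any IUGR-by-modality gap stays in its error variance: a cheap efficiency gain, not a validity error

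*Protocol article*

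**What the plan says.** Under Randomization, "randomization will be stratified (IUGR vs non-IUGR) and by blocks". Under Stratification, the two strata are planned at approximately 10 infants each.

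Under Statistical analysis, the primary endpoint is the within-infant cross-over difference in CSOR change, and "The primary endpoint will be analyzed with a two-tailed matched pairs t-test, after checking of appropriateness of assumptions". The Wilcoxon signed ranks test is the fallback. Neither test carries a stratum term.

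IUGR enters in two other places in that section. One is a secondary comparison of the cross-over difference by IUGR status. The other is an additional multivariable model that adjusts for baseline CSOR, baseline Doppler velocimetry and IUGR. Neither supplies the primary p-value or confidence interval.

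The Discussion frames the IUGR question as open: the study may help to show "if the changes induced by feeding are different in IUGR versus NON IUGR infants". On size, "The expected accrual is about 20 VLBW infants, either IUGR or non-IUGR", and the power statement uses one SD per scenario with no stratum component.

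**The concern.** The primary test is a one-sample test on about 20 cross-over differences. If the mean difference is not the same in IUGR and non-IUGR infants, the spread between strata is counted as random error, although stratum membership is known before randomisation and its split is planned. The standard error is then larger than it needs to be.

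N is set by expected accrual at a single centre over 24 months, so lost power cannot easily be bought back with more infants, and two of the three Table 1 scenarios already stand at or below 80%. The trial studies this same stratum gap as a secondary question, and the model that would remove it from the error term is already planned, but only as an additional analysis.

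**Working it through.** **Inputs.** Two-sided α = 0.05 ("The power calculations below are based on a two-tailed t-test with I-type error α=0.05"); n = 20; cross-over differences 0.07, 0.10 and 0.13 with SDs 0.10, 0.15 and 0.20 (Table 1); strata of 10 and 10 (Stratification). The gap g between strata in the mean cross-over difference is not given in the document and is varied as an assumption.

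**Reproducing Table 1.** Paired t-test, noncentral t with 19 df and noncentrality (difference/SD) × √20:

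| SD | Difference | Stated power | Reproduced |
|---|---|---|---|
| 0.10 | 0.07 | 84% | 84.4% |
| 0.15 | 0.10 | 80% | 80.7% |
| 0.20 | 0.13 | 78% | 78.7% |

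So Table 1 treats σ_CSOR as the SD of the cross-over difference. It does not say whether that SD is within stratum or total, so both readings follow.

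**What the stratum gap does.** With 10 + 10 infants, the expected sample variance of the differences is s² + (g²/4)(20/19), where s is the within-stratum SD. For s = 0.10 and g = 0.10 this is 0.0100 + 0.0026 = 0.0126, an SD of 0.112 instead of 0.10. The mean itself still varies only with s, because the split is fixed. The adjusted test uses s with 18 df.

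**Reading A: the tabled SD is within-stratum.** Adjusted power is 84.1%, 80.5% and 78.5% whatever the gap. Power of the plain paired t-test by simulation:

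| Gap g | SD 0.10, diff. 0.07 | SD 0.15, diff. 0.10 | SD 0.20, diff. 0.13 |
|---|---|---|---|
| 0 | 84.5% | 80.7% | 78.5% |
| 0.25 SD | 84.0% | 80.2% | 78.2% |
| 0.5 SD | 82.7% | 79.0% | 76.9% |
| 1 SD | 77.6% | 73.2% | 70.9% |

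The gain from adjusting is under 2 points up to 0.5 SD and about 6.5 to 8 points at 1 SD. With no gap, the exact figures show the adjusted test 0.2 to 0.3 points worse (84.4 to 84.1, 80.7 to 80.5, 78.7 to 78.5), the cost of one df.

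**Reading B: the tabled SD is total.** Let ρ be the correlation of stratum with the cross-over difference. The within-stratum SD is σ√(1 − ρ²) and the gap is 2ρσ. Gains by simulation with strata fixed at 10 + 10:

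| ρ | Gap in units of σ | Gain from adjusting |
|---|---|---|
| 0.2 | 0.4 | about 1 point |
| 0.3 | 0.6 | 2 to 2.6 points |
| 0.4 | 0.8 | about 4 to 5 points |
| 0.5 | 1.0 | 5.5 to 7.5 points |

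At ρ = 0.5 in the first scenario the figures are 87.2% unadjusted and 92.8% adjusted. On this reading the paired t-test does not fall below Table 1; it forgoes a gain.

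**Type I error, strata fixed at 10 + 10.** The paired t-test rejects in 5.0% of null runs at no gap, 2.9% at a gap of 1 within-stratum SD and 1.5% at 1.5 SD. The adjusted test stays at 5.0%.

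**The case against.** **The protocol does not predict the gap.** A reader might infer that IUGR is expected to change the response, because infants are stratified by it and the Discussion gives a biological rationale. The document does not support this. The secondary aim asks whether responses differ, and the conditional language in the Discussion concerns poor perfusion, feeding tolerance and time to full feeding, not the bolus-versus-continuous contrast. A shared IUGR effect cancels in the pair, and no size or direction is given for an interaction. This stands, and it makes every gain above conditional.

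**Larger gains are not supported.** Comparing Table 1 directly with an adjusted test at ρ = 0.5 (84.4% against 92.7% in the first scenario) suggests 8 to 10 points. That comparison lets the mean vary with the total SD while holding the split at 10 + 10. With the split fixed, the paired t-test does better than Table 1 and the gain is 5.5 to 7.5 points. The scenario is also strong: with a mean of 0.07 and a gap of 0.10, the stratum effects would be 0.02 and 0.12.

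**The mix may be random.** The strata are only approximately 10 and 10, and the article states no quota. If the IUGR share is whatever accrues, the between-stratum spread is genuine sampling variance for the overall VLBW mean. The paired t-test is then correctly sized and the adjusted test is not. With a 50:50 random mix and a true overall mean of zero, its type I error is about 7.0% at ρ = 0.4 and 8.5% at ρ = 0.5. This is arithmetically right, but it needs a random mix and strongly opposed effects in the two strata, whereas the article plans about equal strata. It is a caveat to state, not a reason to leave the stratum out.

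**IUGR is already modelled.** True, but not in the analysis that decides the primary question.

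**Conclusion.** The point holds as a minor efficiency improvement. The primary test ignores a factor used to stratify randomisation, and if the feeding contrast differs between strata, its error term is inflated and it is conservative given the stratum sizes. The size rests on an assumed gap and on how σ_CSOR is read: negligible for small gaps, and roughly 5.5 to 8 points of power when the gap is about one SD.

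It would be wrong to conclude that the planned test is invalid. It does not inflate type I error, its power calculation reproduces, and nothing in the document contradicts it.

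**What to change.** In Statistical analysis, make the primary analysis a linear model of each infant's cross-over CSOR difference on an intercept plus IUGR stratum centred at its sample mean, and test the intercept on 18 df. The estimate is identical to that of the paired t-test; only the error variance and df change. Keep the plain paired t-test as a sensitivity analysis. In Sample size, say whether σ_CSOR is within-stratum or total.

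The cost is a sentence or two of wording, no new data, and one df (0.2 to 0.3 points of power if IUGR is irrelevant). The text should also state the downside: inference is for the planned IUGR/non-IUGR mix, and if that mix is treated as random and the strata differ strongly, the adjusted interval is somewhat too narrow for the overall VLBW mean.

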#### Stratification

Randomization will be stratified in two groups: IUGR infants (approximately 10 children) and NON-IUGR infants (approximately 10 children).

At the achievement of an enteral intake of 100 mL/Kg/day the patients (IUGR and NON IUGR separately) will be randomized in 2 groups: Group A (n=10) will start with bolus administration of nutrition (in 10 minutes); then, after at least 3 hours, they will be fed by the same amount of feed administered as continuous nutrition for 3 hours; Group B (n=10) will start with continuous administration of nutrition for 3 hours followed by a bolus administration of the same amount of feed (in 10 minutes) after at least 3 hours.

The infants of the Group A will be fed with continuous nutrition until the achievement of full enteral feeding (enteral intake of 160 mL/Kg). The infants of the Group B will be fed with 7 or 8 boli/d until the achievement of full enteral feeding.

If, due to clinical instability (i.e. desaturation episodes or bradicardia) during the feeding, a change occurs in the modality of feeding, the results will be analyzed according to the “intention to treat” or the “by treatment” analysis.

All the patients will undergo a baseline evaluation in the first 72 hours of life including: cerebral ultrasound, cardiac ultrasound and abdominal ultrasound.

After birth, in the first 24 hours of life, and in the transitional period, between the 48^th^ and 72^nd^ hours of life, all infants’ intestinal perfusion will be evaluated with NIRS and the echocolordoppler (evaluation of the superior mesenteric artery blood flow) will be performed. The evaluations with NIRS and with the echocolordoppler will be performed under condition of clinical stability (absence of arterial desaturation or instability of cardiocirculatory parameters). Data from NIRS will be collected for 3 hours. Other anamnestic and clinical data will be collected (gestational age, umbilical arterial pH, race, obstetrical anamnesis, mode of delivery, umbilical arterial and venous catheters, patent ductus arteriosus, respiratory distress syndrome, mechanical ventilation, episodes of clinical sepsis). All the infants will be at nothing per os (npo) at the moment of the first two evaluations.

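### The primary paired t-test ignores the randomised feed order and uses pre-feed CSOR only by subtraction; adjusting for both costs about half a point of power, but would not cure carry-over

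*Protocol article*

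**What the plan says.** All places are in the protocol article.

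- Statistical analysis: "The primary endpoint will be analyzed with a two-tailed matched pairs t-test", with the Wilcoxon signed-rank test as fallback. Checking is directed to normality, "since period effect and cross-over effect appear both very unlikely in this study". I read cross-over effect here as carry-over.
- Statistical analysis also defines the response to each feed as the difference between pre- and post-feed CSOR, with the pre-feed value taken 30 minutes before the feed. A secondary generalized linear model of the cross-over difference is planned. The covariates it names are CSOR and Doppler from the first 72 hours of life and IUGR status; sequence, period and pre-feed CSOR are not named.
- Stratification: Group A (n=10) receives bolus (BN) then the 3-hour feed (CN), Group B (n=10) the reverse. The second feed follows after at least 3 hours. The text does not say whether from the start or the end of the first.
- Randomization: within the two IUGR strata, assignment is "based on random permuted blocks of small size, given the limited number of infants expected in each stratum".
- Sample size: "The expected accrual is about 20 VLBW infants, either IUGR or non-IUGR". Power is "based on a two-tailed t-test with I-type error α=0.05".

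**The concern.** A cross-over makes two assumptions that a simple paired study does not: that order has no effect, and that the first feed no longer acts when the second is measured. The plan sets both aside by assertion. The two sequences follow different first feeds, with expected peaks given as 30 minutes and 3 hours. The second pre-feed reading may come 2.5 hours after the end of the first feed. If the gap runs from the start, it may come while a 3-hour feed is still running.

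If there is a period effect, the paired test counts it as random scatter. Power falls when the sequences are balanced, and the estimate shifts when they are not. Separately, subtracting a pre-feed value forces its coefficient to 1, which usually wastes precision compared with estimating it. The first-72-hour covariates cannot do that job: they are constant within an infant, so they cannot adjust for a difference between that infant's two pre-feed values.

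**Working it through.** **Inputs.** From the article: n = 20, two-sided α = 0.05, planned sequences 10:10, Table 1 pairs of σ and difference. Assumed, because the article does not give them: the period effect π, and r, the correlation across infants between the pre-feed BN−CN difference and the post-feed BN−CN difference (equal variances).

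**1. The plan's own figure.** Paired t-test, noncentral t, df = 19, noncentrality = difference/σ × √20. Row 1: 0.07/0.10 × √20 = 3.13. Power for the three rows is 84.4, 80.7 and 78.7%, against 84, 80 and 78% stated. The table reproduces if σ is the SD of the cross-over difference, and σ is used that way below.

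**2. Cost of the two covariates if neither helps.** Same noncentrality, fewer degrees of freedom:

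| Row | df 19 | df 18 | df 17 |
|---|---|---|---|
| 0.10, 0.07 | 84.4% | 84.1% | 83.9% |
| 0.15, 0.10 | 80.7% | 80.5% | 80.2% |
| 0.20, 0.13 | 78.7% | 78.5% | 78.2% |

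**3. Period effect, row 1.** Let d be an infant's BN−CN difference in pre-post change, δ the true effect and π the shift from first to second feed. Then d averages δ − π in Group A and δ + π in Group B, so the mean of d is δ + π(nB − nA)/n.

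- At 10:10 the bias is zero, but the paired variance is inflated to about σ² + π² × 20/19. For π = 0.05 that is 0.0100 + 0.0026 = 0.0126, an apparent SD of 0.112 instead of 0.10. Simulated power of the paired test at π = 0.03, 0.05 and 0.07 is about 82, 77 and 70–71%. The period-adjusted test stays at about 84%.
- At 9:11 and 8:12 with π = 0.05 the bias is 0.05 × 2/20 = 0.005 and 0.05 × 4/20 = 0.010, upward or downward depending on which sequence is larger. Adjustment removes it.
- Simulated type I error of the paired test at π = 0.05 is about 3.0% at 10:10, 3.3% at 9:11 and 4.5% at 8:12.

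**4. Covariate instead of subtraction, row 1, no period effect.** With post- and pre-feed differences of equal variance v, the change score has variance 2v(1 − r) and the covariate model residual variance v(1 − r²). The ratio is (1 + r)/2. Simulating the full model, which includes the cost of estimating the slope:

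| r | 0.3 | 0.5 | 0.8 | 0.9 |
|---|---|---|---|---|
| Covariate model | 94% | 91% | 86% | 83% |
| Paired t-test | 84% | 84% | 84% | 84% |

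The gain is gone by r = 0.9, where about 1 point is lost. As r approaches 1, power tends to about 81.6%.

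**5. Carry-over.** Assume a carry-over of 0.05 after CN only, reaching either the next pre-feed or the next post-feed value, with no true effect. The paired and period-adjusted analyses are both biased by 0.025 (0.05/2), with type I error of about 17% and 19%. At r = 0.5 the covariate model is biased by about 0.012 if only the pre-feed value is affected and 0.025 if only the post-feed value is. If both are affected equally, it is biased by about 0.013, where subtraction has none.

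**The case against.** The best defence is that the paired test is valid under the planned design. At 10:10 a period effect causes no bias and makes the test conservative. That stands.

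A reader might infer from a badly unbalanced split, such as 7:13, that the type I error is inflated. The stated randomisation does not support this. With 20 infants in two strata and fixed blocks of 2, the worst split is 9:11; with blocks of 4 or 6 it is 8:12. With strata of 10 and 10, blocks of 4 give 8:12 with probability 2 × (1/6)² = 5.6%, and blocks of 6 with 2 × (3/15)² = 8%. At those splits, with π = 0.05, the error rate stays below 5%. The bias can also favour the paired test: at 8:12 its power is about 64% or 88% depending on direction, against 83% adjusted. Lost tracings could unbalance the sequences further, but they also reduce n, and the plan provides for imputation.

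It is also fair that a change score is a legitimate, prespecified endpoint, that the secondary model's covariate list is open, that the Discussion calls the study explorative, and that no specific mechanism for a period effect within a day is documented. These points make adjustment an improvement in efficiency rather than a correction of an error. They do not supply the missing support for calling order and carry-over effects improbable.

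**Conclusion.** The point holds as a low-cost improvement to the primary analysis. The article leaves the randomised order and the feed-specific baseline unused, on a statement it does not support. Using both costs about 0.5 point of power in each row of Table 1 if neither covariate helps and the pre-feed slope costs nothing to estimate; counting the slope, the loss is about 1 point at r = 0.9 and close to 3 points as r approaches 1.

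Under the assumed values, row 1 gains about 2 to 14 points from period adjustment (π from 0.03 to 0.07, 10:10) and about 1 to 10 points from covariate adjustment (r from 0.8 down to 0.3). With no period effect and r near 0.9 there is nothing to gain.

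A reader might also infer that the adjusted model protects against carry-over. It does not. In a two-sequence, two-period design period adjustment cannot separate differential carry-over from the treatment effect, and covariate adjustment may reduce that bias, leave it or add to it. Carry-over depends on the separation of the feeds, which the article leaves ambiguous.

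**What to change.** - Make the primary analysis a linear model of the within-infant post-feed CSOR difference (BN−CN), with sequence coded +1/−1 and the pre-feed CSOR difference entered with zero as its reference, so that the intercept is the period-adjusted effect at equal pre-feed values. Keep the paired t-test as a sensitivity analysis.
- Delete the statement that period and carry-over effects are improbable, or give the evidence for it.
- State whether the minimum gap runs from the start or the end of the first feed, and justify why the separation is adequate for the measurement.
- Compare pre-feed CSOR by sequence as a descriptive check only. About 10 infants per sequence give it little power, and it should not decide which analysis is primary.

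The cost is analysis wording, one clarification of the schedule and 2 degrees of freedom. No extra measurements or infants are needed.
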